**Fig 2 pone.0313761.g002:**
[figure not shown]
Study flowchart.

### Group allocation and intervention

Participants in both groups will undergo standardized physiotherapy rehabilitation, delivered through closely supervised sessions. The protocols for these exercises will be adapted from previous relevant studies, ensuring alignment with established practices [9, 28–30]. Exercise prescriptions and progressions will be modified according to the individual needs and impairments of each participant. Examples of the exercise components are illustrated in Table 1. In addition, strategies to improve and monitor adherence to intervention protocols, such as personalized feedback and regular follow-ups, will be implemented. Monitoring procedures will include attendance tracking, session logs, and periodic assessments to ensure participants are following the prescribed regimen.

**Table 1 pone.0313761.t001:** Rehabilitation exercises.

Exercise	Prescription
Range of motion	Prone knee bend; 2 sets, 10 repetitions each Supine alternate knee bend; 2 sets, 10 repetitions
Stretching	Standing quadriceps stretch; 1 set, 3–5 repetitions, 15-second hold each Calf stretch in long sitting; 1 set, 3–5 repetitions, 15-second hold each Supine hamstring stretches; 1 set, 3–5 repetitions, 15-second hold each
Strengthening	Sitting knee extension; Week 1–2, 1 set, 5 repetitions, 5-second hold; Week 3–5, 1 set, 7–10 repetitions, 5-10-second hold; Week 6–8, 2 sets, 10 repetitions, 10-second hold Supine straight leg raises; Week 1–2, 1 set, 5 repetitions, 5-second hold; Week 3–5, 1 set, 7–10 repetitions, 5-10-second hold; Week 6–8, 2 sets, 10 repetitions, 10-second hold Static quadriceps; Week 1–2, 1 set, 5 repetitions, 5-second hold; Week 3–5, 1 set, 7–10 repetitions, 5-10-second hold; Week 6–8, 2 sets, 10 repetitions, 10-second hold Side-lying straight leg raise; Week 1–2, 1 set, 5 repetitions, 5-second hold; Week 3–5, 1 set, 7–10 repetitions, 5-10-second hold; Week 6–8, 2 sets, 10 repetitions, 10-second hold

In addition to the standard physiotherapy rehabilitation, participants in this study will receive acupuncture treatment according to their assigned group: Group 1 Comp-AcuPhysio (n = 25) or Group 2 Man-AcuPhysio (n = 25). The acupuncture treatment protocols are adapted from previous relevant studies [13, 14, 31, 32]. Both acupuncture and physiotherapy treatments for both groups will be administered by a single qualified physiotherapist who is also an acupuncturist and is not involved in outcome assessment. A standard acupuncture session for the treatment of KOA will involve the use of approximately 4 to 12 acupuncture points [13, 32]. Needles will be inserted to appropriate depths (25mm or 40mm), with penetration ranging from 0.8 to 3 cm, and left in place for 20 minutes [13, 32]. The details of the respective group interventions are as follows:

#### Group 1 Comp-AcuPhysio

Participants in this group will receive a 20-minute acupuncture treatment based on a computerized method for identifying point-specific acupuncture using the AcuGraph system (Fig 3), combined with 40 minutes of personalized physiotherapy, totaling 60 minutes per session. The sequence of the interventions will be randomized, and the interventions will be administered once a week for 12 consecutive weeks. Initially, participants will be screened using the AcuGraph system, an electrodermal screening device that assesses energy flow and stress levels by measuring electrical conductance at specific acupuncture points on the skin [33]. This analysis provides information into overall health and meridian imbalances, which are crucial for locating precise acupuncture points on the body [33]. This ensures accurate and effective needle placement, ultimately enhancing the precision of acupuncture treatments to optimize therapeutic outcomes by targeting the body’s vital energy pathways. The computer-generated acupoints specific to each participant will guide the precise points of treatment [33].

**Fig 3 pone.0313761.g003:**
[figure not shown]
Computerized acupuncture point identification using Acugraph system.

#### Group 2 Man-AcuPhysio

Participants in this group will receive a combined treatment of acupuncture and personalized physiotherapy, lasting a total of 60 minutes per session. Each acupuncture treatment will be approximately 20 minutes long, tailored according to the acupuncturist’s manual preferences. To ensure blinding of participants, a placebo Acugraph analysis will be used to conceal group allocation. Based on acupuncturist’s manual preferences, commonly used acupoints include Yanglingquan (GB34), Yinlingquan (SP9), Dubi (ST35), and Neixiyan (EX-LE4) [34]. Depending on the patient’s condition, the acupuncturist may add two or more local acupuncture points based on their professional judgment (Table 2) [34]. The acupuncturist will conduct a thorough assessment of each patient’s condition, considering any contraindications and maintaining a sterile environment. The acupuncture points selected will specifically target knee pain and arthritis [13, 32]. These points may vary based on the pathway of Qi flow and include both proximal and distal points around the antero-medial and antero-lateral parts of the knee joint [13, 32]. Additionally, acupoints located on the stomach and spleen meridian channels, which pass through the knee area, may be used [13, 32].

**Table 2 pone.0313761.t002:** Examples of manual acupuncture points selection.

Acupoint	Name	Location
Fixed acupoints	Yanglingquan (GB34)	On the lateral side of the lower leg, in the depression anterior and inferior to the head of the fibula
	Yinlingquan (SP9)	On the medial side of the shank, at the depression posterior and inferior to the medial condyle of the tibia.
	Dubi (ST35)	Between the lower edge of the patella and the upper tip of the tibia, at the midpoint of the patella ligament
	Neixiyan (EX-LE4)	In the depression located on the medial side of the patellar ligament
Optional: anteromedial parts knee joint	Xuehai (SP10)	On the anterolateral aspect of thigh, on the bulge of vastus medialis muscle, 2 cun superior to the medial end of the base of patella
Optional: anterolateral parts knee joint	Liangqiu (ST34)	On the anterolateral aspect of thigh, between vastus lateralis muscle and lateral border of rectus femoris tendon, 2 cun superior of the base of patella
Optional: stomach meridian channels that pass through the knee area	Zusanli (ST36)	3 cun directly below ST35, and one finger breadth lateral to the anterior border of tibial
	Fenglong (ST40)	On the anterolateral aspect of leg, lateral border of tibialis anterior muscle, 8 cun superior to the prominence of lateral malleolus
Optional: spleen meridian channels that pass through the knee area	Sanyinjiao (SP6)	On the tibial aspect of the leg, posterior to the medial border of the tibial, 3 cun superior to the prominence of medial malleolus
	Gongsun (SP4)	On the medial aspect of the foot, anteroinferior to the base of the 1^st^ metatarsal bone, at the border between red and white flesh

Note: 1 cun (~20 mm) is the width of the interphalangeal joint of the patient’s thumb.

### Blinding

Screening, recruitment, and randomization of participants will be conducted by a research assistant uninvolved in the intervention or outcome assessment, ensuring unbiased processes [35]. Outcomes will be assessed by a blinded assessor not involved in the intervention. The James Blinding Index (JBI) will be used to evaluate blinding success from the participants’ perspective [35].

### Safety consideration

Adverse events related to acupuncture, including pain, bleeding, fainting, or other severe incidents, will be promptly addressed and meticulously documented in the case report form [14]. Strict safety protocols will be adhered to throughout the procedure, including: (i) ensuring treatments are administered by qualified acupuncturists and therapists to guarantee safe and proficient delivery, and (ii) implementing rigorous infection control measures. These measures encompass hand hygiene, the use of disposable needles, proper skin preparation, maintenance of a sterile environment, appropriate needle handling, glove usage, and thorough patient screening [36, 37]. In addition, interim analyses will be conducted at predefined intervals to monitor safety and efficacy. These analyses will evaluate the incidence of adverse events and the overall effectiveness of the treatment. Any relevant incident will be discussed among the research team, and decisions will be made based on consensus. Recommendations regarding the continuation, modification, or termination of the trial will be based on predefined criteria, including unacceptable adverse event rates or clear evidence of benefit or harm.

The safety of acupuncture in the management of musculoskeletal pain has been well-documented in the literature, with minimal adverse events reported [14, 15, 38]. Therefore, a data and safety monitoring committee (DSMC) will not be appointed for this trial, given its low-risk nature. This approach is consistent with comparable trials such as those conducted by Wang et al. (2024) and Pang et al. (2022), where no DSMC was deemed necessary in randomized studies of acupuncture for KOA [39, 40]. Nonetheless, all safety events, including adverse effects, will be carefully recorded, and participant monitoring will remain thorough to ensure ongoing safety.

### Outcome measures and assessment interval

Outcome measures will be assessed at two intervals: (i) baseline (pre-intervention) and (ii) immediately post-intervention. All data, including consent forms, sociodemographic information, and outcome measures, will be collected using hardcopy clinical research forms (CRFs). Data from the CRFs will be transferred into an Excel spreadsheet for storage and further analysis. All hardcopy documents will be kept in a secure location, and electronic files will be protected on a password-secured computer with restricted access. These research records, in both physical and electronic formats, will be retained for a minimum of five years following the study’s publication.

**Knee Injury and Osteoarthritis Outcome Score (KOOS):** The KOOS questionnaire will be administered to evaluate participants’ perceptions of knee function and osteoarthritis-related symptoms. It consists of five subscales: pain (nine items), symptoms (seven items), activities of daily living function (17 items), sport and recreation function (five items), and quality of life (four items) [27]. The test-retest reliability of KOOS is excellent, with intraclass correlation coefficients ranging from 0.91 to 0.99 [27]. Each item is scored on a five-point Likert scale ranging from 0 (no problems) to 4 (extreme problems). The individual subscale scores are calculated by summing the responses and transforming the total into a 0–100 scale. A score of 0 indicates severe knee-related issues, while a score of 100 reflects no knee-related problems [24, 27]. Apart from calculating the total KOOS score, individual subscales for each of the domains will be calculated and analyzed separately to provide a detailed assessment of different aspects of knee function [24]. This approach allows us to capture domain-specific improvements or changes in response to the intervention, ensuring a comprehensive evaluation of KOA outcomes [24].**Active knee flexion range of motion (AKF):** Knee flexion will be measured using a long-arm universal goniometer. The stationary arm of the goniometer will be aligned with the greater trochanter along the outer thigh, and the other arm with the lateral malleolus of the ankle. The goniometer has a high reliability value, with an intraclass correlation coefficient of 0.997 for knee flexion in subjects with knee impairments [41]. Normal knee flexion ranges from 0 degrees (knee in full extension) to approximately 140 degrees (maximal knee flexion). Higher ROM values within this range reflect greater knee flexion capacity, whereas lower values suggest restricted knee movement [42].**Timed Up and Go Test (TUG):** The TUG test assesses functional mobility by measuring the time taken to stand up from a chair, walk 3 meters, turn, and return to sit down [43]. In this study, the average time of three trials will be documented to improve accuracy. The time taken to complete the task is recorded, with shorter times indicating better functional mobility, balance, and lower fall risk [43]. A completion time exceeding 14 seconds suggests significant impairment in functional mobility and is associated with an elevated risk of falls [43]. The minimal detectable change for this test is 1.10 seconds [43]. The TUG test demonstrates high reliability and validity for mild to moderate KOA, with intra-rater and inter-rater reliability values of 0.97 (95% CI, 0.95–0.98) and 0.96 (95% CI, 0.94–0.97), respectively [43].**Visual Analog Scale (VAS):** The VAS is a subjective measurement tool commonly used to assess pain intensity. It is determined using a linear scale spanning from 0 to 10 centimeters. On this scale, 0 indicates the absence of pain, while 10 signifies severe pain, with varying degrees of pain intensity in between of it [44]. Participants indicate their pain levels by marking positions along the line. The reliability of the VAS for assessing chronic pain in clinical settings is excellent, with a test-retest intraclass correlation coefficient of 0.97 [44].**The Short Form 36 Health Survey (SF-36):** The Short Form 36 Health Survey (SF-36): The SF-36 Health Survey (SF-36) is a comprehensive questionnaire consisting of 36 items designed to assess various aspects of health and well-being, covering eight primary domains of overall health status. Patients are asked to respond based on their recent experiences, typically over the past week, providing a snapshot of their current health [45]. Response options include formats such as “yes/no,” “never/sometimes/often/always,” or Likert scales ranging from “excellent” to “poor.” Each domain is scored from 0 to 100, with higher scores indicating better health or functioning in that area [45]. The domains are as follows: (i) physical functioning, (ii) role limitations due to physical health, (iii) role limitations due to emotional problems, (iv) energy levels and fatigue, (v) psychological well-being, (vi) social functioning, (vii) pain intensity and interference with activities, and (viii) overall health perceptions [45]. The SF-36 also provides two overarching summary scores: the Physical Component Summary (PCS) and the Mental Component Summary (MCS), which represent the physical and mental health dimensions, respectively [45]. Higher scores in these summaries denote better overall health status in the respective areas.**Personal Integrated Energetics—Acugraph System:** This system measures and analyzes the energetic status of acupuncture meridians. Each wedge of the circle in the Personal Integrated Energetics (PIE) chart represents one meridian pathway, where those shown in green are balanced and functioning properly [33]. The PIE score includes a complete analysis of all meridian pathways and reflects the overall health of the meridian energy system (Fig 4) [33]. A perfect score of 100 reflects complete balance and unimpeded flow of Qi energy, while a lower score indicates various imbalances that need to be addressed [33].

**Fig 4 pone.0313761.g004:**
[figure not shown]
Example of a Personal Integrated Energetics score based on an analysis using the Acugraph system.

### Data analysis

Data entry and storage will follow strict protocols to ensure quality and confidentiality. Double data entry will be employed to reduce errors, and range checks will be conducted to detect any outliers or inconsistencies [46]. All data will be encrypted and stored in a password-protected system with limited access, complying with privacy regulations [46]. The presentation and reporting of the study’s findings will adhere to CONSORT reporting guidelines, ensuring transparency and consistency in the reporting of the trial. The data analysis will be conducted by a researcher who is blinded to group allocation, and in consultation with an expert statistician. Measurement data will be tested for normality. If data conform to a normal distribution, they will undergo t-test analysis, while non-normally distributed data will be analyzed using the Mann-Whitney U test. For normally distributed data, the mean and standard deviation will be calculated, and for non-normal data, the median and percentages will be presented.

In this study, an intention-to-treat analysis will be employed. This approach will include all eligible randomised participants initially allocated to the study, regardless of their adherence to the protocol. ITT analysis is chosen because it preserves the benefits of randomization, maintains the baseline comparability of groups, and provides a more conservative estimate of the treatment effect, thereby increasing the external validity of the findings [47]. Missing data will be handled using the multiple imputation technique, which involves creating multiple datasets by imputing missing values through statistical models [48]. The results from these datasets will then be combined to account for the uncertainty caused by the missing data [48].

Additionally, a per-protocol analysis will be conducted to compare findings from participants who adhered strictly to the protocol [47]. This comparison will help assess any differences in outcomes between the two approaches [47]. To examine differences between the both groups over time, a repeated measures ANOVA will be employed to assess changes in KOOS, AKF, TUG, VAS, SF-36, and PIE scores over time (time main effect) and to evaluate whether these changes over time differed between the two groups (group-by-time interaction). Additionally, to assess the extent of variation between groups, the effect size of each variable will be calculated using Cohen’s d, where values of 0.2, 0.5, and 0.8 indicate small, medium, and large effects, respectively [26]. In addition, subgroup analysis will be performed based on key factors such as age groups, BMI, and disease severity (mild vs. moderate), as these variables are considered important contributors to outcomes in KOA. The analysis will help identify whether the intervention effects vary across these subgroups.

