**Methods:**

A randomized, double-blind controlled trial will be conducted with 50 participants diagnosed with mild to moderate KOA. Participants will be randomly assigned to one of two groups: Group 1 Comp-AcuPhysio (n = 25), receiving Acugraph-guided acupuncture with physiotherapy, or Group 2 Man-AcuPhysio (n = 25), receiving manually selected acupuncture with physiotherapy. Both groups will undergo 12 weekly treatment sessions, each lasting 60 minutes. Outcome measures, including the Knee Injury and Osteoarthritis Outcome Score, active knee flexion range, Timed Up and Go test, Visual Analog Scale for pain, Short Form-36 health survey, and Personal Integrated Energetics score, will be assessed at baseline and immediately post-intervention. An intention-to-treat analysis will be applied. Changes from baseline to 12 weeks will be analyzed using repeated measures analysis of variance for both within-group and between-group comparisons.

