### Sample size calculation

The sample size was calculated using G*Power software version 3.1.9.7, with a focus on achieving a robust estimate for detecting clinically meaningful changes. Specifically, a minimum clinically important difference (MCID) of 11.1 points, with a standard deviation (SD) of 3.8 points, was used based on established values for the primary outcome, the total Knee Injury and Osteoarthritis Outcome Score (KOOS) [24]. This estimation considered a power of 80%, an effect size of 0.2, a significance level of 5%, and an anticipated dropout rate of 20% [25, 26]. Consequently, the total calculated sample size was 50 participants, evenly divided into two groups of 25 participants each. KOOS was selected as the primary outcome measure for this study due to its comprehensive assessment of key domains relevant to KOA, including pain, symptoms, activities of daily living, sport and recreation, and quality of life [27]. The tool has been widely validated in populations with KOA and is sensitive to changes following interventions, making it an appropriate and robust measure for capturing patient-reported outcomes in this context [27].

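### The normality-based choice between t-test and Mann-Whitney is not reconciled with the repeated-measures ANOVA set for KOOS and the other outcomes

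*Protocol article*

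**What the plan says.** Four places in the protocol article bear on this.

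- **Data analysis, first paragraph.** "Measurement data will be tested for normality", and then: "If data conform to a normal distribution, they will undergo t-test analysis, while non-normally distributed data will be analyzed using the Mann-Whitney U test". No outcome, time point or contrast (score or change) is named. A rule on summaries follows, under which "for non-normal data, the median and percentages will be presented".
- **Data analysis, later paragraph.** "a repeated measures ANOVA will be employed to assess changes in KOOS, AKF, TUG, VAS, SF-36, and PIE scores over time (time main effect"), and also "to evaluate whether these changes over time differed between the two groups (group-by-time interaction"). No exception is made for non-normal data.
- **Abstract, Methods.** "Changes from baseline to 12 weeks will be analyzed using repeated measures analysis of variance for both within-group and between-group comparisons". No other between-group test is mentioned.
- **Outcome measures and assessment interval.** "Outcome measures will be assessed at two intervals: (i) baseline (pre-intervention) and (ii) immediately post-intervention". There are therefore two measurements per participant.

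The Sample size calculation section makes total KOOS the primary outcome and gives an MCID of 11.1 points. The Data analysis section also plans an intention-to-treat analysis with multiple imputation and combined results.

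**The concern.** Mann-Whitney U compares two independent groups, so the first rule describes a between-group test, and the six named outcomes are the trial's main measurement data. Read as written, the rule reaches KOOS. If KOOS then fails the normality test, one sentence leads to Mann-Whitney and another still leads to ANOVA. Nothing ranks them.

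Three things are at stake:

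- **Which result counts.** An analyst who follows both instructions has two p-values for the primary outcome and no written rule for choosing.
- **What is estimated.** A Mann-Whitney test gives no mean KOOS difference to set against the MCID. It also supplies no estimate and standard error of the kind that Rubin's rules pool after multiple imputation.
- **How skewed scores are described.** Percentages do not describe the spread of a continuous score.

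**Working it through.** The plan gives no figure on this point, so there is none to reproduce. The check is of what follows under each reading.

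**Inputs from the article:** 25 per arm, 20% dropout, 5% significance level, two time points. Completers per arm: 25 × (1 − 0.20) = 20.

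**Assumptions, not in the article:** two-sided testing; pre/post correlation ρ of 0.3, 0.5 or 0.7; normal or lognormal scores; normality judged by Shapiro-Wilk at 5% in each arm.

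**Step 1: when the two tests coincide.** With two time points, the group-by-time F equals the square of the two-sample t on change scores. A numerical check gave F = 0.9626 and t² = 0.9626. A t-test on change is therefore the ANOVA interaction test. A t-test on post-treatment scores is a different test: with equal variances, the post score and the change correlate at √((1 − ρ)/2), which is 0.5 at ρ = 0.5.

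**Step 2: type I error under no effect.** Simulated trials with 20 or 25 per arm, 10,000 per setting:

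| Procedure | Rejection rate |
|---|---|
| ANOVA interaction alone | 4.4-5.1% |
| Normality test, then t or Mann-Whitney, alone | 4.6-5.6% |
| Either one counts; t/Mann-Whitney on post scores | 8.4-9.7% |
| Either one counts; t/Mann-Whitney on change, normal data | 5.0-5.4% |
| Either one counts; t/Mann-Whitney on change, lognormal data | 6.0-6.4% |

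A second set (20 per arm, 6,000 trials per setting) gave 9.2-10.4% for either-counts on post scores. With stronger skew (log-scale SD of 1), either-counts on change reached 6.8%. Rounded, the ranges are 8-11% and 5-7%. For scale, two independent 5% tests give 1 − 0.95² = 9.75%, and two exact 5% tests cannot exceed 10% together. The top of the first range therefore reflects simulation noise and slightly liberal component tests with skewed data.

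**Step 3: how often the pre-test triggers.** With normal data, testing each arm at 5% flags 1 − 0.95² = 9.75% of trials. That follows from the assumed rule and is not a property of the sample size.

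**Step 4: how often the routes disagree.** With an assumed true difference of 0.8 SD, 20 per arm and the t/Mann-Whitney test on post scores, the two routes differ on significance in about 29% of trials.

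**Step 5: what a baseline-adjusted analysis offers.** In SD² units, the change score has variance 2(1 − ρ) and the ANCOVA residual has 1 − ρ². The ratio is (1 + ρ)/2, which is at most 1. For 0.8 SD, 20 per arm and ρ = 0.5:

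- Interaction test: noncentrality 0.8 × √(20/2) ÷ √(2 × 0.5) = 2.53; power 0.69 on 38 df.
- ANCOVA: noncentrality 2.53 ÷ √0.75 = 2.92; power about 0.81 by formula on 37 df, and 0.80-0.81 in simulation.

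By the same formulas the powers are 0.55 against 0.73 at ρ = 0.3, and 0.89 against 0.93 at ρ = 0.7.

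**The case against.** The strongest reply is that the article does point to one test. The Abstract names only repeated-measures ANOVA, and the Data analysis section assigns all six outcomes to it by name. The normality sentence names no outcome and is followed directly by the rule for summaries, so it may have been meant for baseline or descriptive comparisons. This largely stands. A reader might infer that the primary test is left wholly open; the documents do not support that. Applying the normality rule to KOOS is an inference, though a natural one, because the text does not confine the rule.

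A reader might also infer that the plan inflates the error rate. It does so only if both analyses are run on KOOS and a positive result from either may be claimed, which the article does not say. Nor is the pre-test itself the cause, since used alone it holds the level at about 5%.

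Two further objections are that this is detail for an SAP and that ANCOVA is a preference. The first fails: these are two published instructions that diverge, not an omission. The second is fair as far as it goes. Naming repeated-measures ANOVA as the single primary test would also remove the conflict; ANCOVA is recommended on its merits.

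**Conclusion.** The point holds in a limited form. The article states two between-group procedures without saying how they relate, and they part company if KOOS is judged non-normal. The weight of the text favours repeated-measures ANOVA, which leaves the normality rule as the passage to remove or confine.

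The effect on the error rate is conditional: about 8-11% if both tests are run, either may count and the t/Mann-Whitney test uses post-treatment scores; about 5-7% if it uses change scores. These figures rest on the assumed Shapiro-Wilk rule, correlations and distributions. The summary of non-normal data by median and percentages is a separate small reporting error that does not affect inference.

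**What to change.** 1. Name one pre-specified primary between-group analysis for total KOOS, and apply the same one to the other continuous outcomes. A baseline-adjusted ANCOVA of the 12-week score is preferable: baseline is already collected, in large samples it is at least as powerful as the two-time-point interaction test, and it gives a mean difference that can be set against the MCID and pooled after imputation.
2. Delete the normality-based switch, or limit it explicitly to baseline description or a labelled sensitivity analysis.
3. Summarise skewed scores by median and interquartile range.
4. Align the Abstract with whichever analysis is named.

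The cost is a few sentences and a small change to the analysis. Data collection and trial conduct do not change.

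### With one baseline and one post-treatment value, the planned repeated-measures ANOVA interaction is a t-test on change scores: valid, but usually less precise than ANCOVA adjusting for baseline

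*Protocol article*

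**What the plan says.** Under Outcome measures and assessment interval: "Outcome measures will be assessed at two intervals: (i) baseline (pre-intervention) and (ii) immediately post-intervention". There is no intermediate or later assessment.

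Under Data analysis, the comparison over time is fixed for all six outcomes: "a repeated measures ANOVA will be employed to assess changes in KOOS, AKF, TUG, VAS, SF-36, and PIE scores over time". Its between-group part is "to evaluate whether these changes over time differed between the two groups (group-by-time interaction". The Methods paragraph of the Abstract agrees: "Changes from baseline to 12 weeks will be analyzed using repeated measures analysis of variance for both within-group and between-group comparisons".

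The only other tests named for comparing measurements come earlier in Data analysis: "If data conform to a normal distribution, they will undergo t-test analysis, while non-normally distributed data will be analyzed using the Mann-Whitney U test". The protocol nowhere mentions ANCOVA or the baseline value as a covariate. Missing data are to be multiply imputed within an intention-to-treat analysis, and Cohen's d is to be calculated in addition.

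**The concern.** Repeated-measures ANOVA sounds like a model that makes full use of longitudinal data. With a single follow-up it does not. The between-group term reduces to a comparison of mean change, which fixes the weight on baseline at exactly 1 and does not estimate it from the data. When the regression slope of follow-up on baseline is below 1, as it usually is, subtracting the whole baseline adds noise that ANCOVA would remove.

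The stake is precision. The trial randomizes 50 people and allows for 20% dropout. Both arms receive acupuncture plus the same physiotherapy programme, so the contrast is between two active treatments. The same choice applies to the primary outcome, total KOOS, and to every secondary outcome. The method is stated in both the Abstract and the main text, so it is not a detail left open for a separate analysis plan.

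**Working it through.** **Inputs from the protocol.** Two arms of 25; two assessment times; 20% dropout, so 50 × 0.8 = 40 completers, 20 per arm.

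**Inputs assumed.** The baseline-to-follow-up correlation ρ (range 0.3 to 0.95) and the ratio k of baseline SD to follow-up SD. The protocol gives neither.

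The protocol states no figure for the precision of this analysis, so there is none to reproduce. Its sample size of 50 does not enter the argument except as N.

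**Step 1: the identity.** With two times, the interaction contrast is (post − pre in group 1) − (post − pre in group 2), which is the difference in mean change. Its error term comes from the within-group variance of the change, on N − 2 degrees of freedom. Hence F(interaction) = t² on change scores. On one simulated data set with 25 per arm, F = 2.8435 and t² = 2.8435.

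**Step 2: relative precision with equal SDs (k = 1).** With common variance s², the per-person variances are:
- change score: 2(1 − ρ)s²
- ANCOVA, large sample: (1 − ρ²)s²
- ratio: (1 − ρ²) / [2(1 − ρ)] = (1 + ρ)/2

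Estimating the slope multiplies the ANCOVA variance by 1 + 1/(N − 4). At N = 40 this is 37/36 = 1.028.

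| ρ (assumed) | (1 + ρ)/2 | with slope estimated, N = 40 |
|---|---|---|
| 0.3 | 0.65 | 0.67 |
| 0.5 | 0.75 | 0.77 |
| 0.7 | 0.85 | 0.87 |
| 0.9 | 0.95 | 0.98 |
| 0.95 | 0.975 | 1.002 |

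With all 50 analysed the factor is 47/46, and the first four ratios become 0.66, 0.77, 0.87 and 0.97. Simulation with 20,000 replicates at N = 40 gave 0.67, 0.77, 0.87 and 0.98, with no bias in either estimator.

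**Step 3: unequal SDs.** The general large-sample ratio is (1 − ρ²) / (1 + k² − 2ρk). At ρ = 0.7:
- k = 0.8: 0.51 / (1 + 0.64 − 1.12) = 0.51/0.52 = 0.98
- k = 1.2: 0.51 / (1 + 1.44 − 1.68) = 0.51/0.76 = 0.67

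The ratio reaches 1 when ρ = k, that is, when the slope of follow-up on baseline is 1.

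**Step 4: power, for illustration only.** Assume a true difference of 0.8 follow-up SD, 20 per arm, k = 1 and two-sided 5%. The noncentrality is 0.8/√(2V/20). V = 2(1 − ρ) for change (38 df) and (1 − ρ²) × 37/36 for ANCOVA (37 df).

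| ρ | V change | V ANCOVA | noncentrality | power, change → ANCOVA |
|---|---|---|---|---|
| 0.3 | 1.40 | 0.935 | 2.14 → 2.62 | 55% → 72% |
| 0.5 | 1.00 | 0.771 | 2.53 → 2.88 | 69% → 80% |
| 0.7 | 0.60 | 0.524 | 3.27 → 3.49 | 89% → 93% |

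**The case against.** The strongest reply is that nothing here is an error. The interaction test is valid and unbiased under randomization, the Abstract and main text agree on it, and it is in common use. That stands in full: the point is lost efficiency only.

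The size is also open to challenge, and rightly so. The simple ratio needs equal SDs at the two times, and ρ is unknown. The 0.8 SD in the power illustration is not the trial's design value; the protocol uses 0.8 only as the label for a large Cohen's d. The sample size section gives "a minimum clinically important difference (MCID) of 11.1 points, with a standard deviation (SD) of 3.8 points" (11.1/3.8 = 2.92 SD) and also an effect size of 0.2. If either is read as a difference in follow-up SD units, with 20 per arm and k = 1, the choice of analysis barely moves power. At 2.92 both methods are near 100%. At 0.2 power goes from 8.2% to 9.8% (ρ = 0.3), 9.5% to 10.8% (0.5) and 12.5% to 13.6% (0.7). The narrower confidence interval remains in every case, because the variance ratio does not depend on the true difference.

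A reader might go further in four ways that the protocol does not support:
- *That ANCOVA wins whenever ρ is below 1.* At N = 40 with equal SDs the ratio is already 1.002 at ρ = 0.95.
- *That chance baseline imbalance, through regression to the mean, is a second harm.* Averaged over randomizations, it is the same excess variance that the ratio already counts.
- *That Cohen's d replaces a difference in KOOS points.* The protocol introduces d as an addition, plans means and SDs, and commits to CONSORT reporting.
- *That a fixed number of patients is being lost.* At ρ = 0.5 the large-sample ratio 0.75 corresponds to 1/0.75 = 1.33 times the sample, but only under that ρ and equal SDs.

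**Conclusion.** The point holds as one of efficiency. The equivalence to a change-score t-test is exact and rests on no assumption beyond two groups, two times and complete pairs. That ANCOVA is at least as precise in large samples is also general. At about 20 completers per arm with equal SDs, the expected reduction in variance is roughly 33%, 23%, 13% and 2% at ρ = 0.3, 0.5, 0.7 and 0.9, and nothing near 0.95. With unequal SDs it can be smaller or larger. These percentages depend on values the protocol does not give, so confidence is high in the identity and in the usual direction, and only moderate in the size. The planned test would not give a biased or invalid answer. The change should be made because the trial is small and the possible loss from ANCOVA is negligible (a factor of 37/36 in variance and one degree of freedom), while the possible gain is material.

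**What to change.** In Data analysis, and correspondingly in the Abstract:
- Make the primary between-group analysis an ANCOVA of post-intervention total KOOS on treatment group and baseline total KOOS.
- Report the adjusted mean difference with its 95% CI in KOOS points, so that it can be read against the 11.1-point MCID.
- Use the same model for AKF, TUG, VAS, SF-36 and PIE, each with its own baseline.
- Fit the model in each imputed data set and pool the group coefficient by Rubin's rules.
- Keep Cohen's d, if wanted, as a supplement.

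The cost is one degree of freedom and one paragraph of text. No extra data, visits or participants are needed.
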